### Measures

We will record the following demographic and other characteristics of the participants: gender, age, workplace, work period, participation in previous training on anaphylactic shock, being a mentor or tutor, being a teacher, participation in emergency or off-duty care, and previous experience with patients with anaphylactic shock (number of cases).

The WCQ scale provides insight into the processes or strategies of stress management. It contains 66 statements measured on the following scale: 0: none at all; 1: partial; 2: extensive; 3: overwhelming. The statements measure 8 dimensions of stress management: confrontation, distance, self-control, seeking social support, taking responsibility, escape/avoidance, planned problem solving, and positive reassessment. The validity of the construct of the WCQ scale lies in the fact that the research results are consistent with the following theoretical assumptions: (1) Coping involves both problem-oriented and emotionally regulating strategies, and (2) coping is a process. This means that the way stress is handled depends on the demands of the situation and the changes that occur over time [22].

The evaluation scale will consist of several criteria against which we will judge compliance with the guidelines for handling a patient with anaphylactic shock and the safe performance of the procedures. It will also include criteria for assessing the safety of the procedure. Each criterion will be rated as successfully completed or unsuccessfully completed, and the score on the evaluation scale will be the percentage of successfully completed criteria; this will be our primary outcome. Its dichotomous version (which will only be classified as successful if all criteria are successfully completed) will be our secondary outcome. In addition, we will analyze the criteria used to assess the safety of the procedures. Only those participants who meet all safety criteria will be classified as participants who treat the patient in a safe way.

### Intervention

All participants will participate in a 1-day training program consisting of a lecture on emergency care and anaphylactic shock as well as exercises in manual dexterity (aspiration, airway management, alternative airway management, artificial respiration, chest compressions, safe defibrillation, oxygen application, use of medication during emergency care). The test group will receive education on anaphylactic shock in AR. Training with AR is a scenario for the management of a patient with anaphylactic shock. When the head-mounted display is put on, a woman with symptoms of anaphylactic shock that gradually worsen can be seen. Her breathing becomes difficult, an urticarial rash appears, and she says she does not feel well and cannot breathe. When she is asked questions, she answers. The participant must then take the necessary steps to treat this patient correctly; otherwise, the augmented patient will die.

AR intervention represents a combination of standardized and evaluated medical procedures corresponding to a specific medical event (in our case, anaphylactic shock) and digital support id software. Development of an AR intervention consists of (1) defining a medical event, (2) analysis and documentation of crucial parameters (eg, patient type, symptoms, procedures, measurements, medication, equipment involved [eg, monitor, pulse oximeter], decision tree, execution process, and time perspective), (3) defining targeted users or user groups, (4) creation of the use case scenario, (5) defining the expected (un)wanted outcome in the form of standardized results (points achieved, success rate in percentages), (6) software development (environment creation including all 3D assets, animations, sounds, and user interactions), and (7) integration of all elements described into the most believable realistic, holistic experience producing adequate levels of stress in regards to the potential real case scenario.
The AR intervention was developed by a group of medical experts (doctor, nurse, and instructor) and information technology experts (user experience engineers, 3D artists, designers, AR developers, and product specialists).
The AR intervention will be delivered in the form of software as a service, meaning an application supporting available devices for distributing AR content. Add-ons to the application will be web space for user management and tracking of participant success (pass rate).
Trained instructors for emergency medicine education with simulations will deliver the intervention.

### Technical Information

#### Hardware

The primary type of device used for the execution of an AR intervention now is HoloLens, a standalone computer supporting comprehensive 3D rendering, unlimited user movement, voice control, and hand tracking. Any additional controllers will be used. HoloLens supports communication with Internet of Things devices (id sensors or other supportive elements) and the cloud, offering additional computing resources for multiple user experiences (eg, debriefing).

#### Software

The HoloLens uses a Windows Holographic platform. The device’s interface uses gaze input (head tracking), gestures (bloom, air tap, air tap and hold), and voice commands. Three gestures are used to interact with the AR environment: (1) bloom: upward-facing palm, starting with fingertips together, then spreading fingers outward — used for application start-up and closure; (2) air tap (tap and release): with the dorsal aspect of the user’s hand facing them, raising and flexing the index finger (ie, up, down, and up again) in a pinch-like fashion (press and release) — used for selecting an operation; (3) air tap and hold: raising and flexing the index finger to the thumb and motioning the pressed fingers together (press and hold) — used in the user’s 3D space (ie, up, then down) for manipulation of selected objects.

### Ethical Considerations

In this study**,** we will determine the effectiveness of a new teaching method in a controlled environment without health risks. Possible side effects of using AR could be dizziness, headaches, and nausea. Therefore, participants with known similar reactions to similar environments will not be included in the study. Recordings from the study will be used for research purposes only and will be stored on a secure server. The use of a standardized patient in a clinical environment may cause stressful situations. To avoid this, participants are informed immediately before the start of the simulation with the standardized patient that this is a simulation and not a real situation. All participants will be offered a free 1-day training with AR at the end of the study.

### Statistical Analysis

#### Power Calculation

Sufficient sample size to detect a difference between the test and control groups in the score of the evaluation scale (primary outcome) using a 2-tailed independent *t* test was determined using power analysis. For α of .05 and 80% power to reject the null hypothesis of equal group means, when the population mean difference is 10 points (considered clinically relevant) and population SD of both groups is 20 points, a sample size of 128 (64 per group) is needed. The SD of 20 was used based on the results of a study on the use of case-based simulations with high-fidelity mannequins in teaching and retention of emergency management team skills [18]. In that study, the SD of the evaluation scores was <20 for all scenarios. To account for dropouts, we plan to recruit 150 participants.

For the secondary outcome (dichotomous version of the score of the evaluation scale), we performed power analysis using the planned sample size of 128 (64 per group). A chi-square test with α of .05 achieves 80% power to reject the null hypothesis of equal group proportions of successful assessments if the population difference between the group proportions is 21%-25%, where the proportion of successful assessments in the control group is assumed to be between 15% and 40%.

Sample size calculations were conducted using PASS 2019 Power Analysis and Sample Size Software [24].

#### Statistical Methods

We will summarize categorical variables with frequencies and percentages, and we will summarize numerical variables with means and SDs or medians and IQRs in the case of asymmetric distributions. To highlight the differences between the groups at baseline, we will use the chi-squared test or Fisher exact test (if more than 20% of the expected frequencies are below 5) for categorical variables and independent samples *t* test or Mann-Whitney U test (in the case of asymmetric distributions) for numerical variables.

For the comparison of groups after 1 year (primary time point), we plan to use a *t* test for independent samples (or Mann-Whitney U test) for the evaluation scale score (primary outcome) and a chi-squared test (or Fisher exact test) for its dichotomous version (secondary outcome) and for the safety criteria. To compare groups at all time points (right after the intervention, after 1 month, and after 1 year) efficiently in one model, we will use appropriate mixed-effects regression models, which are able to appropriately take into account repeated measurements of the same patient. The power for detecting differences between groups with these models is even higher than with independent *t* tests or chi-square tests that were used in the power analysis.

To evaluate the short-term and long-term effectiveness of coping with stress, only the following dimensions will be included in the analysis: confrontation, distance, self-control, seeking social support, taking responsibility, escape/avoidance, planned problem solving, and positive reassessment. We will sum items to provide each of these scales. For each scale, groups will be compared using a linear mixed-effects regression model.

A *P* value <.05 will be considered as statistically significant.

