#### Phase Two

The flow of the study is presented in Figure 1. The study is expected to last for 1 year. Before the intervention, we will assess the baseline characteristics of the participants. All participants will complete the questionnaire on demographic and other data (see Measures). They will also complete the Folkman-Lazarus Ways of Coping Questionnaire (WCQ; please see Measures for more information) [22]. The baseline knowledge, skills, and competencies of the participants regarding the management of a patient with anaphylactic shock will be assessed through a simulation based on the developed scenario using a high-fidelity simulator in a learning environment (a classroom). The participants will perform the simulation in a group of 3; the other 2 members of the group will be educated trainers. They will follow the leadership of the individual participant and not engage in actions until instructed by the participant. The simulation will be video recorded. The recordings will be independently assessed by 3 experts that will not be aware of the participant’s group allocation (blinded), based on the developed evaluation scale. They will harmonize their assessment and produce a single result. This will be in the form of a numeric outcome (primary outcome result) and in a binary form (successful/not successful).

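### The primary 1-year comparison is a valid but unadjusted test that leaves the baseline simulation score unused, giving up precision and correction for the baseline imbalance actually drawn

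*Protocol article*

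**What the plan says.** All places are in the protocol article.

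- **Baseline measurement** (Procedures and Data Collection, Phase Two): "The baseline knowledge, skills, and competencies of the participants regarding the management of a patient with anaphylactic shock will be assessed through a simulation". The simulation is recorded, and three experts unaware of allocation rate it on the evaluation scale. They agree a single numeric result, which is the form of the primary outcome. The later assessments use the same scenario, and 1 year is the primary time point.
- **Primary analysis** (Statistical Methods): at 1 year, a *t* "test for independent samples (or Mann-Whitney U test) for the evaluation scale score (primary outcome"). Neither test uses the baseline score.
- **Repeated-measures analysis** (same section): mixed-effects models are named separately, with the purpose "To compare groups at all time points (right after the intervention, after 1 month, and after 1 year) efficiently in one model". Baseline is not mentioned.
- **Stated use of baseline data** (same section): significance tests between groups, introduced with the words "To highlight the differences between the groups at baseline". No adjustment is tied to them.
- **Sample size** (Power Calculation): based on the same unadjusted two-sided *t* test.

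**The concern.** The trial pays for a recorded, blinded, expert-rated baseline value of its own primary outcome, and the named primary test then ignores it. Family physicians are likely to differ in emergency skill before training: the Measures section records previous anaphylaxis training, cases seen and emergency duty. If part of that difference persists to 1 year, it sits in the error term of the unadjusted test and widens the confidence interval. If the groups also happen to differ in baseline skill, a share of that difference passes into the estimated AR effect. Testing baseline differences for significance displays an imbalance but does not remove it from the estimate.

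**Working it through.** **Inputs from the article (Power Calculation).** Two-sided significance level 0.05; target power 80%; a true difference of 10 points between the groups; an SD of 20 points, given as "population SD of both groups is 20 points"; and 64 participants in each arm.

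**Assumption.** The correlation r between baseline and 1-year score is not stated, so a range is shown.

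**Step 1: reproduce the plan's figure.** The standard error of the group difference is 20 × √(2/64) = 3.54. The noncentrality is 10/3.54 = 2.83. The two-sided noncentral *t* with 126 degrees of freedom gives 80.1% power at 64 per group and 79.5% at 63. The stated 128 is therefore correct for the planned test.

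**Step 2: adjust for baseline.** With a linear relation and the same r and SD in both groups, the residual SD is 20 × √(1 − r²). The degrees of freedom fall by one, to 2n − 3 = 125. For example, at r = 0.5 the residual SD is 20 × √0.75 = 17.32, the SE is 17.32 × √(2/64) = 3.06, the noncentrality is 10/3.06 = 3.27, and power is 90.0%.

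| r (assumed) | Variance saved (r²) | SE of difference | Power at 64 per group | Total N for 80% power |
|---|---|---|---|---|
| 0 | 0% | 3.54 | 80.1% | 128 |
| 0.2 | 4% | 3.46 | 81.7% | 124 |
| 0.3 | 9% | 3.37 | 83.7% | 118 |
| 0.5 | 25% | 3.06 | 90.0% | 98 |
| 0.6 | 36% | 2.83 | 93.9% | 84 |

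The first row shows the price of adjusting when baseline predicts nothing: power is still 80.1%.

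**Step 3: chance imbalance.** Assume that the baseline SD is also 20; the article gives none. The baseline difference between groups then has SE 3.54 and exceeds 5 points in either direction in about 16% of randomizations (5/3.54 = 1.41). With equal SDs, a baseline difference D shifts the expected unadjusted 1-year difference by r × D. For D = 5 the shift is 1.5 points at r = 0.3 and 2.5 points at r = 0.5, against a target of 10.

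Given that 5-point imbalance and no true effect, the unadjusted difference is centred on 5r with SE 3.54 × √(1 − r²), and is declared significant beyond 1.96 × 3.54 = 6.93 points. That happens with probability about 6.0% at r = 0.3 and 7.5% at r = 0.5. Averaged over all randomizations the rate is 5%.

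**The case against.** The strongest reply is that nothing here is an error. Under randomization the two-sample *t* test is unbiased with 5% type I error, chance imbalance is already allowed for in its standard error, and the sample size was computed for exactly this test. All of that stands. A reader might infer that the planned result would be biased or the trial underpowered; the article's own figures show neither.

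The second objection is that r could be low. Baseline is on a high-fidelity simulator in a classroom, while the 1-year assessment is with a standardized patient at the workplace. Between them lie a training day for both groups, debriefings, and a year in which real cases or further courses may intervene (Limitations). The article also expects participants to adapt to simulation mainly in their second one (Discussion, Methodology), so the first score may partly reflect unfamiliarity. This stands as a limit on size: at r = 0.2 the gain is 81.7 − 80.1 = 1.6 percentage points. It is not a reason against adjusting, since the cost is one degree of freedom.

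Third, the mixed models might include baseline. The text lists the times at which groups are compared and is silent on covariates, and a model with baseline as covariate would list the same three times. So the inference that baseline goes unused in every analysis is not supported. This does not rescue the primary comparison, which is named separately as a *t* test or Mann-Whitney test.

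Fourth, a reader might extend the point to the coping questionnaire scales or to the baseline significance tests. For the scales the article says only that a linear mixed model will be used, and silence on baseline is not exclusion. No stated analysis decision depends on the baseline tests, so removing them would change no result.

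**Conclusion.** The point holds as a recommendation to improve a choice that the article states; it is not a detail left to an analysis plan. The named primary test is valid and delivers its planned 80% power, but it discards a blinded baseline value of the primary outcome. At 64 per group the gain ranges from 1.6 percentage points of power at r = 0.2 to 13.8 (93.9 − 80.1) at r = 0.6. The estimate would also be corrected for the baseline difference actually drawn.

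That no adjustment appears in the named test is certain from the text. The size of the benefit is not: it rests on an assumed r, on a linear relation with equal SDs of 20 in the groups at 1 year, and, for the imbalance figures, on a baseline SD of 20.

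**What to change.** In Statistical Methods, name as the primary analysis an ANCOVA of the 1-year evaluation score on group and baseline score, or the 1-year group contrast from a mixed model that includes the baseline score. Report the adjusted difference in points with a 95% CI. Keep the unadjusted *t* test (or Mann-Whitney U test) as a sensitivity analysis. The sample size need not change, since it is already sufficient for the unadjusted test.

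The cost is about one sentence of text and one degree of freedom. No new data, participants or procedures are needed. The change should be fixed before 1-year results are seen by group.

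### The primary test at 1 year is not fixed: the rank-test alternative does not test the 10-point mean difference on which the trial was sized

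*Protocol article*

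**What the plan says.** All references are to the protocol article.

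- **Primary test (Statistical Methods).** At 1 year, the primary time point, groups are compared by an independent-samples t test "or Mann-Whitney U test) for the evaluation scale score (primary outcome"). The sentence does not say when the second test replaces the first.
- **Nearest condition (same section).** Asymmetry is mentioned for descriptive summaries and for baseline comparisons, the latter using the "Mann-Whitney U test (in the case of asymmetric distributions) for numerical variables". It is not repeated for the primary outcome.
- **Sample size (Power Calculation).** The trial was sized "using a 2-tailed independent" t test: "For α of .05 and 80% power to reject the null hypothesis of equal group means", with "population mean difference is 10 points (considered clinically relevant") and an SD of 20 in both groups. This gives 64 per group.
- **Score (Measures).** "the score on the evaluation scale will be the percentage of successfully completed criteria; this will be our primary outcome". Its dichotomous version is the one "which will only be classified as successful if all criteria are successfully completed".
- **Secondary power (Power Calculation).** "the proportion of successful assessments in the control group is assumed to be between 15% and 40" per cent, with 80% power for a difference of 21 to 25 percentage points.
- **Mixed models (Statistical Methods).** Mixed-effects models are also planned, to compare the groups over all post-intervention assessments together.

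**The concern.** Two tests are named for one primary comparison, and they answer different questions. The t test asks whether mean percentages of completed criteria differ, which is the quantity given a threshold of clinical relevance. Mann-Whitney asks whether a score from one group tends to exceed a score from the other. It yields no mean difference to set against 10 points. A shift estimate could accompany it, but the article names none, and such an estimate is not a difference in means.

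With a roughly symmetric score the distinction would matter little. Here the score is bounded at 100, and the plan's own success rates put a sizeable share of participants exactly at that bound. The rank test is then likely to be chosen, and rank and mean comparisons can diverge. At stake are which hypothesis the trial tests and whether its main result can be read on the scale used to justify its size.

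**Working it through.** **1. The plan's sample size.** Inputs: difference 10, SD 20, two-sided alpha 0.05, power 80%. Normal approximation: n per group = 2 × (1.96 + 0.8416)² × 20² / 10² = 2 × 7.849 × 4 = 62.8, so 63. The exact noncentral t gives power 0.795 at 63 and 0.801 at 64 per group. The stated 64 per group (128) reproduces.

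**2. Share at the maximum.** Success is a score of exactly 100%. Controls: 15% to 40%. Test group, if the detectable difference were true: 15 + 21 = 36% to 40 + 25 = 65%.

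**3. Would the fallback be used?** The article gives neither a distribution nor a switching rule, so both are assumed here.

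- *Normal score censored at 0 and 100, control SD 20.* Control skewness is -0.54, -0.83 and -1.27 with 15%, 25% and 40% at 100. Switching when a skewness or Shapiro-Wilk test has P < 0.05 in either arm, 97% to 100% of simulated trials switch when the groups differ. With no difference, 61% to 100% switch by the skewness test and over 99% by Shapiro-Wilk.
- *Beta-shaped score, identical arms.* A skewness test triggers in 99% of trials with 40% at 100, but in only 9% with 15% at 100.

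Use of the fallback is therefore likely over much of the range but depends on shape and rule at the low end.

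**4. Power and type I error.** 64 per arm, censored-normal model, 4,000 trials per case:

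| Controls at 100% | t test power, 10-point difference | Mann-Whitney power | Type I error, Shapiro-Wilk switch |
|---|---|---|---|
| 15% | 85.1% | 85.3% | 5.2% |
| 25% | 88.8% | 90.2% | 5.1% |
| 40% | 93.0% | 95.1% | 5.3% |

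With normal data and a standardised difference of 10/20 = 0.5, Mann-Whitney has about 78% power, against 80.1% for the t test. If the smaller of the two P values were taken, type I error would be about 5.8% to 6.8%.

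**5. Equal means, unequal shares at 100%.** 64 per arm, scores in 5-point steps:

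| Share at 100%, control vs test | Shape | Mann-Whitney rejects | Welch rejects |
|---|---|---|---|
| 40% vs 65% | mean 82, two separate runs | 24% and 26% | 5.1% and 4.4% |
| 40% vs 65% | mean 82, SD 10 below 100 | 13% | – |
| 40% vs 65% | mean 87, SD 10 below 100 | 20% | – |
| 25% vs 47% | two separate runs | 8.7% and 7.8% | 4.7% (second run) |
| 25% vs 47% | SD 10 below 100 | 6.5% | – |
| 15% vs 36% | SD 10 below 100 | 5.1% | – |

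A dash means that no Welch figure is available for that row. A further set of shapes, with means equal or nearly equal, gave roughly 6% to 32% for Mann-Whitney and about 5% for Welch throughout.

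**6. Is the fallback needed to protect the level?** With identical distributions and 15%, 40% or 65% at 100%, Welch rejects in 4.8%, 5.1% and 4.8% of trials. At this sample size it is not.

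**The case against.** Several objections have force.

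- **Asymmetry as the trigger.** A reader might infer that asymmetry is the plan's stated trigger for the primary test. It is not: that wording covers summaries and baseline comparisons. A detailed switching rule could sit in an analysis plan not shown, so its absence is not the point. What stands is that the article itself names two primary tests with different hypotheses.
- **The ceiling as a forecast.** The 15% to 40% is a range for the secondary power calculation, and 21 to 25 points is a detectable difference, not an expected effect. The evaluation scale was still being developed. The 36% to 65% in the test group is therefore conditional.
- **Power.** A reader might infer that the switch undermines the stated power. The calculations do not support that: 128 reproduces, and the two tests have similar power under the ceiling model.
- **The 24% figure.** It comes from an extreme case. With mean 82 and 65% at 100, the rest must average (82 - 65) / 0.35 = 48.6, against (82 - 40) / 0.60 = 70 for controls. The test-arm SD is then at least √(0.65 × 0.35) × (100 - 48.6) = 24.5, above the plan's 20. It shows that the tests can disagree, not how often they would. The case with mean 87, where the SD stays below 20, still gives 20%.
- **The mixed model.** For the score it would estimate mean differences, including at 1 year, so the report need not be confined to a rank P value. But the t test or Mann-Whitney is what the article names for the primary time point.

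**Conclusion.** The point holds in a limited form. The primary test is not uniquely fixed, and one of the two tests named does not address the mean difference on which the trial was sized. The plan's own success rates make a skewed score, and so the rank test, likely, though not certain at the low end.

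The damage is to the hypothesis tested and the effect reported, not to the sample size. Type I error stays near 5% under a fixed rule and reaches about 6% to 7% only if the smaller P value is picked. Where means are equal or nearly so but shares at 100% differ, Mann-Whitney rejects in roughly 5% to 30% of simulated trials, against about 5% for Welch. Such rejections are not errors for Mann-Whitney's own hypothesis; they mislead only if read as a difference in mean score. The range rests on assumed score shapes, since the article gives none, and its upper part belongs to the highest success rates.

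**What to change.** Before any 1-year data are seen, name one primary analysis: the difference in mean evaluation-scale score at 1 year. Preferably estimate it from a linear model, or the 1-year contrast of the planned mixed model, adjusted for the baseline simulation score that Procedures and Data Collection (Phase Two) already collects. Report it in points with a heteroscedasticity-robust or bootstrap 95% CI, whatever the shape of the distribution. Keep Mann-Whitney as a labelled sensitivity analysis.

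The essential change, one named mean-based analysis, needs only a short revision of Statistical Methods and no new data; 128 still suffices. Baseline adjustment is a further improvement and not needed to resolve the mismatch. The small downside is that a rank test can be slightly more powerful for some skewed shapes (95.1% against 93.0% in the most skewed power case above).

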**Figure 1 figure1:**
[figure not shown]
Schematic presentation of the randomized controlled trial in phase two of the study. WCQ: Ways of Coping Questionnaire.

After the intervention (see Intervention), the participants will once again perform the simulation with a high-fidelity simulator and complete the WCQ, which will be followed by a debriefing. We will use a structured tool for debriefing called TALK (Target, Analysis, Learning Points, Key Actions), which is designed to guide structured team self-debriefing after any learning event in clinical environments. It promotes a supportive culture of learning and patient safety [23]. The simulations will be again video recorded, and the recordings will be assessed by experts as already described.

Both groups will be assessed again at 1 month and 1 year after the intervention, using the WCQ scale and simulation. This time, the simulation will be performed in the participant’s workplace and with a standardized patient, followed by a debriefing. The scenario of the simulation will be the same as before. Again, simulations will be video recorded; experts, as already described, will assess the recordings.

The short-term effect will be measured using performance immediately and 1 month after the intervention, while the long-term effect will be measured 1 year after the intervention, which will also be our primary time point.

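### The unqualified claim that the mixed models have higher power than the t and chi-square tests does not hold in general, and for the 1-year contrast they have essentially the same power

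*Protocol article*

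**What the plan says.** Under Procedures and Data Collection, Phase Two, the protocol article sets the primary time point: "while the long-term effect will be measured 1 year after the intervention, which will also be our primary time point".

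The Power Calculation section sizes the trial for one two-group comparison of the evaluation score by a two-tailed independent t test. It applies "when the population mean difference is 10 points (considered clinically relevant) and population SD of both groups is 20 points" and concludes that "a sample size of 128 (64 per group) is needed". For losses it adds: "To account for dropouts, we plan to recruit 150 participants".

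Statistical Methods assigns the 1-year comparison to a t test (or Mann-Whitney U test) for the score, and to a chi-squared or Fisher exact test for the dichotomous version and the safety criteria. It then adds mixed-effects models comparing the groups right after the intervention, at 1 month and at 1 year. Of these it says: "The power for detecting differences between groups with these models is even higher than with independent" t tests or the chi-square tests of the power analysis. It does not say which contrast, covariates or within-person correlation this refers to. A baseline simulation score is collected (Phase Two), but Statistical Methods does not name it as a model term.

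**The concern.** The sentence compares the models' power directly with the power analysis, and that analysis concerns a single difference in means. The natural counterpart in a repeated-measures model is the group difference at 1 year. Earlier post-intervention visits add no information to that difference when everyone is measured at 1 year and the model lets the group effect vary by visit.

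What is at stake is the understanding of the trial's power. The t test only just reaches its target (0.801 at 64 per group, 0.795 at 63). Someone who takes the sentence at face value may think the models supply a margin that they do not supply for the 1-year question. Without a named contrast, it is also open which result from the model is meant to carry that extra power.

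**Working it through.** **Inputs from the protocol article.** Two-sided α 0.05, difference 10, SD 20, 64 per group, 150 recruited (75 per group if split equally), and three post-intervention visits with 1 year primary. **Assumed, because not given:** exchangeable within-person correlation ρ = 0.3, 0.5 or 0.7.

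**1. The plan's own figures.** The noncentral t distribution gives power 0.795 at 63 per group and 0.801 at 64, so 128 is reproduced. For the dichotomous outcome at 64 per group, the difference detectable with 80% power runs from 21.5 percentage points (control 15%) to 24.5 (control 40%), in line with the stated 21% to 25%.

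**2. The 1-year contrast, complete data.**
- t test: SE = 20 × √(2/64) = 3.5355. By the normal approximation, power = Φ(10/3.5355 − 1.96) = 0.807.
- Mixed model with group-by-time means: generalised least squares gives SE 3.5355 at each of the three correlations, so power is again 0.807.
- Fitted check at ρ = 0.5: in 200 simulated trials with a random-intercept model, the largest gap between the two estimates was about 1e-12, and the mean SE was 3.513 for both.
- In 20,000 simulated trials, using the closed form of the random-intercept model, power was 0.806 (mixed model) against 0.805 (t test).

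With a random intercept the SE uses a variance pooled over visits. It therefore matches the t test's SE on average, not in every sample.

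**3. Where power differs.** Write 2 × 20²/64 = 12.5 for the variance of a single-visit difference.
- *Common effect over the three visits:* SE = √(12.5 × (1 + 2ρ)/3).
- *Baseline adjustment at 1 year:* SE = √(12.5 × (1 − ρ²)).
- *11 of 75 per group missing only the 1-year visit:* SE = √(800 × [(1 − R²)/64 + R²/75]), where R² = 2ρ²/(1 + ρ).
- *Joint 3-df test of any group difference, constant 10-point effect:* noncentral chi-square with noncentrality (10/SE)², taking SE from the common-effect formula.

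| ρ | 1-year contrast, complete data | Common effect: SE, power | Baseline-adjusted: SE, power | 1-year visit missed by 11 per group: SE, power | Joint 3-df test: power |
|---|---|---|---|---|---|
| 0.3 | 0.807 | 2.582, 0.97 | 3.373, 0.84 | 3.499, 0.815 | 0.92 |
| 0.5 | 0.807 | 2.887, 0.93 | 3.062, 0.90 | 3.448, 0.826 | 0.84 |
| 0.7 | 0.807 | 3.162, 0.89 | 2.525, 0.98 | 3.383, 0.840 | 0.76 |

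The joint test falls below the t test at ρ = 0.7 even when the effect is the same at every visit. Whether a model-based test gains or loses power thus depends on the contrast and the correlation.

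**4. Not computed.** The power of a mixed model for the dichotomous outcome was not evaluated. A logistic mixed model estimates a conditional odds ratio, so step 2 does not carry over to it.

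**The case against.** The sentence does not name the 1-year contrast. The article gives that comparison to the t test and introduces the models for comparing groups at all visits. Read as a statement about an effect shared across visits, it is true when the effect is constant. That stands, but the sentence sets no such condition. A constant effect is not stated anywhere, the assessment moves from classroom simulator to workplace standardized patient, and the Discussion (Methodology) warns that mastery can fade over weeks and months.

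Complete data is also not what the authors expect, since they plan for dropout. This stands too. When only the 1-year visit is missed, earlier scores recover some power even for the 1-year contrast, though people lost at every visit contribute nothing.

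Finally, the article says only that appropriate models will be used, and a fuller analysis plan may include baseline. That is fair, and the absence of a full model specification is not the criticism. The criticism is of a positive claim made without the conditions that it needs.

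A reader might go further and infer that the trial is underpowered, or that any loss beyond 150 − 128 = 22 participants takes power below 80% with no cushion. The documents do not support this. The sample size rests on the t test, which is the planned 1-year test, and no participants were saved on the strength of the sentence. If those lost at 1 year attended both earlier visits, the model matches the 64-per-group benchmark with about 63, 60 or 54 per group at 1 year (ρ = 0.3, 0.5, 0.7), a loss of roughly 24, 30 or 42 from 150. Nor does a 5% rejection rate for the group-by-time interaction under a constant effect show low power: no interaction exists in that case, so 5% is the type I error rate.

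**Conclusion.** The concern holds as a wrong general statement, with limited consequence. For the 1-year contrast on the continuous score, with group-by-time means over the three listed visits and complete data, the gain in power over the t test is essentially zero. This does not depend on the assumed correlation. The gains in the table do depend on it, and each needs a condition that the sentence omits. For the dichotomous outcome and the safety criteria the claim is unsupported in the document; it has not been shown to be false. The planned 1-year test, the 128 and the 150 are untouched.

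**What to change.** Delete the sentence, or replace it with wording such as: *For the 1-year contrast the model has about the same power as the t test, apart from gains from baseline adjustment or from partly missing 1-year data.* Make no power claim for the binary outcomes unless a calculation supports it.

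Include the baseline simulation score as a covariate in both the 1-year comparison and the mixed model. It is already collected, so this needs no new data and makes a gain real. The size of the gain depends on how well a classroom simulator score predicts a workplace score a year later, so the lower end of the range is the safer expectation.

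Name the 1-year group contrast as the decisive result from the model, ahead of any averaged, joint or interaction test.

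The cost is one sentence restated, one covariate added and one contrast named. The only loss is an unsupported claim of extra power.
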